## Background

Prostate cancer (PCa) is the leading male cancer in the United Kingdom and a principal cause of cancer-related mortality with around 46,700 cases diagnosed in 2014 [1]. The incidence of PCa has increased markedly over the past 20 years and it is projected to rise by 12% between 2014 and 2035 to 233 per 100,000 males [1]. Common treatments options for localised prostate cancer are external beam radiation therapy (EBRT), brachytherapy (BRT) or radical prostatectomy [2].

However, biochemical recurrence (BCR) following radiotherapy occurs in 25% of treated men within 5 years, manifesting as a rising prostate-specific-antigen (PSA) [3]. This is strictly a biochemical diagnosis, most commonly defined as an increase in serum PSA of 2.0 ng/ mL above the nadir [4]. Once a PSA relapse has been diagnosed, it is important to determine whether the recurrence has developed at local or distant sites and hence BCR following therapy often initiates an imaging-based assessment of local and metastatic disease in patients.

Local recurrence of PCa is investigated by prostate multi-parametric magnetic resonance imaging (mp-MRI) [5] whilst metastatic disease is assessed by multi-modality imaging. The standard workup to detect PCa metastases usually includes ^99m^Tc bone scan and chest/abdomen/pelvis (CT-CAP) scan (or where available ^18^F-choline or ^68^Ga-PSMA PET-CT) [6].

The workup to exclude distant metastasis is of greatest significance as it is estimated that about half of those who develop radio-recurrent disease have distant metastases (either overt on imaging or micro-metastases) [7]. It is also believed that up to 50% of men who are considered to be free of metastases by conventional staging methods have micro-metastatic disease [8]. This is reflected in prostate cancer recurrence following EBRT or BRT, where biochemical relapse commonly precedes clinical detection of metastases by an average of 7–8 years [9].

Earlier detection of metastatic disease could be the key to better patient stratification and well-informed patient management either by opting for active surveillance or local salvage for low risk individuals or offering systemic therapy at an earlier time point to a high-risk population [10].

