### Health economic data collection

Data collection for the health economic analysis will be primarily concerned with cost data associated with the diagnosis and treatment of metastatic prostate cancer. Routinely collected administrative data from UCLH will be used to determine the relevant costs associated with the diagnostics test. To determine the consequence of detected metastatic disease on the treatment pathway, clinical experts will be interviewed, and patient notes will be reviewed noting changes to medication, radiotherapy, surgery, outpatient visits, inpatient visits and day cases, where possible. Data from existing trials such as STAMPEDE [24] and FORECAST [7] will be used to inform other economic parameters such as the health-related quality of life as these are not being collected in LOCATE.

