**Fig. 2 Fig2:**
[figure not shown]
Enhanced reference standard derivation flowchart. FN: False Negative, TP: True Positive, FP: False Positive, TN: True Negative, UK: Unknown, ADT: Androgen Deprivation Therapy

Patients will be divided into those with and without metastases evident on conventional imaging. For those with metastases (left arm of Fig. 2), concordant positive WB-MRI findings will be deemed to be true positive and discordant WB-MRI findings will be considered to be false negative.

For patients without metastases on conventional imaging (right arm of Fig. 2), clinical and biochemical follow-up together with changes between baseline and follow-up WB-MRI will be used to enhance the reference standard.

Where baseline WB-MRI was negative and concordant with conventional imaging, the presence of new lesions (at follow-up WB-MRI ± repeat routine imaging) coupled with a PSA rise over the 12-month will classify the baseline WB-MRI as false negative, i.e. disease was present but not visualised. Whereas the absence of new lesions regardless of PSA status over the 12-month follow-up period will confer baseline WB-MRI true negative status.

For positive findings on baseline WB-MRI discordant with conventional imaging, the baseline WB-MRI will be deemed true positive when a new lesion declared itself (on follow-up WB-MRI ± routine imaging) or the visualised lesion on baseline WB-MRI enlarged (on follow-up WB-MRI); and this was accompanied with a PSA rise within the 12-month follow-up period. Whereas, the baseline WB-MRI will be deemed false positive when the lesion evident at WB-MRI resolved or reduced in size at follow-up (in the absence of systemic therapy) regardless of PSA change. Lesions that resolved following systemic therapy (which is initiated in the 1-year follow-up period irrespective of negative conventional baseline imaging) with corresponding decrease in PSA will be classified as true positive.

Finally, patients with negative baseline conventional imaging with discordant lesion and PSA changes over the 12-month follow-up (i.e. lesion size/number increase without corresponding PSA increase) will be classified as unknown.

The section below describes the thresholds for PSA and lesion size changes, and they will be interpreted in the context of treatment intervention and subsequent treatment response or progression.

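### The false-positive rule excepts only systemic therapy, so a true lesion shrunk or removed by local or regional treatment would be scored as a WB-MRI false positive

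*Protocol article*

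**What the plan says.** All the rules at issue are in the Protocol article, mostly under Derivation of enhanced reference standard, in the text after Figure 2. They concern men whose conventional imaging is negative.

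- **False positive.** A lesion seen on baseline WB-MRI is a false positive if it "resolved or reduced in size at follow-up (in the absence of systemic therapy) regardless of PSA change".
- **True positive after treatment.** The one treatment-related route begins "Lesions that resolved following systemic therapy (which is initiated in the 1-year follow-up period irrespective of negative conventional baseline imaging" and also requires a fall in PSA.
- **True positive by growth.** The lesion enlarges or a new one appears, "and this was accompanied with a PSA rise within the 12-month follow-up period".
- **Unknown.** This applies where there is "lesion size/number increase without corresponding PSA increase".
- **General clause.** Of the PSA and size thresholds, the section says that "they will be interpreted in the context of treatment intervention and subsequent treatment response or progression".

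Four other places bear on the point:

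- The Background says that earlier detection could guide management "either by opting for active surveillance or local salvage for low risk individuals".
- Health economic data collection has patient notes reviewed, "noting changes to medication, radiotherapy, surgery, outpatient visits, inpatient visits and day cases", where possible.
- Initial WB-MRI scan withholds the baseline read from the clinical team, apart from significant additional or incidental findings.
- 12-month follow-up WB-MRI sends discrepant findings to a consensus panel, which decides lesion status.

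**The concern.** The systemic-therapy exception concedes that treatment can shrink real disease, so that shrinkage after treatment is no proof that a lesion was benign. Radiotherapy to a field containing the lesion, or surgery that removes it, has the same effect, yet neither is excepted. The rule also disregards PSA, so even a PSA fall that fits treated cancer cannot rescue the classification.

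A second, conditional problem concerns PSA. Where salvage of a prostatic recurrence lowers PSA, a lesion elsewhere may grow or appear without any PSA rise. The man is then unknown rather than diseased.

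Men positive on WB-MRI alone are the ones who can produce a sensitivity advantage over conventional imaging. Moving a few of them to false positive lowers both sensitivity and specificity. Moving them to unknown may remove them from the comparison. Either way, the accuracy estimate would depend partly on how often non-systemic treatment is used, which is not a property of the test.

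**Working it through.** **1. The rules side by side (conventional imaging negative)**

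| Course of a true lesion after local or regional treatment | Class as written |
|---|---|
| WB-MRI-positive lesion in the field or resection; shrinks or disappears; no systemic therapy | False positive, whatever PSA does |
| WB-MRI-positive lesion outside the field; grows; PSA rises | True positive |
| WB-MRI-positive lesion outside the field; grows; PSA does not rise | Unknown |
| Baseline WB-MRI negative; new lesion; PSA rises | False negative |
| Baseline WB-MRI negative; new lesion; PSA does not rise | Unknown |

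A negative baseline WB-MRI with no new lesion stays true negative whatever the PSA. Suppressed PSA can therefore cost a man a diseased verdict but not a true-negative one.

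The general clause governs how thresholds are read and assigns no class. The threshold list describes shrinkage as response without limiting it to systemic therapy, whereas the class rule calls the same shrinkage a false positive unless systemic therapy was given. These texts need reconciling.

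**2. The plan's own figure**

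The Sample size section gives 130 men, 50% prevalence, a 20-point sensitivity difference, 90% power and a 0.05 cut-off. Diseased men: 130 × 0.5 = 65. Net WB-MRI-only true positives: 0.20 × 65 = 13.

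The section states no discordant proportion ψ. With a two-sided McNemar approximation,

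n = (z_a√ψ + z_b√(ψ − d²))² / d².

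At an assumed ψ = 0.26 and d = 0.20: (1.96 × 0.510 + 1.282 × 0.469)² / 0.04 ≈ 64.0, which the exact calculation rounds up to 65 diseased men, or 130 in all. So 130 is attainable under an unstated assumption. It is neither confirmed nor refuted, and the present point does not depend on it.

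**3. Illustration of size**

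Assumptions: 65 diseased and 65 non-diseased men; 13 WB-MRI-only true positives with no reverse discordance; no false positives otherwise; unknowns, if that is the class, excluded. Let k of the 13 be affected.

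- Sensitivity gain = (13 − k)/(65 − k), whether the k men become false positives or are dropped.
- Specificity loss if scored false positive = k/(65 + k).

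| k | Gain, points | Specificity loss, points |
|---|---|---|
| 0 | 13/65 = 20.0 | 0 |
| 1 | 12/64 = 18.8 | 1/66 = 1.5 |
| 3 | 10/62 = 16.1 | 3/68 = 4.4 |
| 4 | 9/61 = 14.8 | 4/69 = 5.8 |
| 6 | 7/59 = 11.9 | 6/71 = 8.5 |

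With some reverse discordance the gain column is unchanged, because it depends only on the net 13. With a true specificity of 95% instead of 100%, the loss is slightly smaller: at k = 3, from 0.950 to 0.95 × 65/68 = 0.908.

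**4. Effect on power**

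With assumed sensitivities of 70% and 50% and ψ = 0.25, power = Φ((d√n − z_a√ψ)/√(ψ − d²)), with d, n and ψ recomputed after k men are removed. It falls from 0.92 (k = 0) to 0.89 (k = 1), 0.80 (k = 3) and 0.67 (k = 5).

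**The case against.** The strongest reply is that this will be rare. Clinicians do not see the baseline WB-MRI read and conventional imaging is negative, so a WB-MRI-only lesion would not normally be targeted. Treating the prostate does not remove a node or a distant metastasis. The error needs a lesion that happens to lie in a regional field or resection, or one disclosed as a significant finding. The Background names local salvage only in general terms and does not describe pelvic radiotherapy or nodal surgery in these men. All of this stands, and it limits the size.

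The second reply is that the text leaves room for judgement: the treatment-context clause is not confined to systemic therapy, PSA progression is measured from baseline or start of treatment, and a panel settles discrepant lesions. Figure 2 is not shown; its legend names only androgen deprivation therapy. This too stands, but none of the available text gives the class of a lesion exposed to non-systemic treatment, and the rule that does give one calls it false positive.

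A reader might go further in three ways that the document does not support:

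- That every true-positive or false-negative verdict in these men needs a PSA rise. The systemic-therapy route reaches true positive with a PSA fall.
- That any lesion growing after salvage becomes unknown. With a PSA rise it is classed normally.
- That the treatment information needed is already in hand. The notes review serves the economic analysis, is done where possible, and mentions neither dates nor fields.

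**Conclusion.** The false-positive rule is wrong as written for a narrow group: conventionally negative, WB-MRI-positive men whose lesion lay within a local or regional treatment and who had no systemic therapy. The general clause and the panel do not correct it. The route to unknown through suppressed PSA is a further, conditional weakness.

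The 1 to 6 affected men, with a gain of 18.8 to 11.9 points and a specificity loss of 1.5 to 8.5 points, are an illustration. They rest on 13 WB-MRI-only true positives among 65 diseased men, no other false positives, and unknowns being excluded. The document gives no count, and the true number is probably small. A reader might infer that the primary comparison is seriously compromised; nothing in the document establishes that. This is a correction worth making before analysis, not a defect that undermines the design.

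**What to change.** 1. In Derivation of enhanced reference standard, extend the false-positive condition to the absence of systemic therapy and of any local or regional treatment that could have included the lesion.
2. Class a lesion that shrinks or disappears after such treatment as unknown, unless routine pathology from that treatment settles it.
3. Record local or regional treatment during follow-up on the adjudication form, with enough detail to judge whether it could have included the lesion.
4. Reconcile the class rules with the treatment-context clause and the response and progression definitions that follow it, including how PSA change is read in men salvaged during follow-up.
5. Report a sensitivity analysis that classes the affected men both ways. In the illustration the gain would then be bracketed by 13/65 = 20.0 points (all true positive) and (13 − k)/(65 − k) (all false positive).

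The cost is rewording, one adjudication item and some extra review of notes; no scans, patients or changes to care are needed. The downside is a few more unknowns. The change removes the specificity bias, but if unknowns are excluded it does not by itself restore the sensitivity gain, which is why step 5 is needed. The Study status section expects full analysis to begin shortly, so the rule should be settled before then.

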PSA progression defined as ≥25% and ≥ 2 ng/mL increase in PSA recorded at least 12 weeks from baseline or start of treatment and confirmed on a 2nd reading 3–4 weeks later as previously defined [26, 27].

PSA response defined as ≥50% decline from baseline or start of treatment and confirmed on a 2nd reading 3–4 weeks later [28, 29].

Nodal size change Increase of ≥2 mm and decrease of ≥3 mm in short axis diameter on contrast enhanced mDixon sequence will be considered true change (progression and response respectively) rather than a measurement variation, with a 95% confidence interval. (Based on unpublished data from repeatability studies carried out as part of the LOCATE trial).

Bone lesion (disease progression) ≥ 25% increase in size (sum of short and long axes diameters) of lesions on CT, or MRI [30, 31].

Bone lesion (treatment response) ≥ 50% decrease in size (sum of short and long axes diameters) of lesions on CT/ MRI or normalisation of signal intensity on MRI [30, 31].

Soft tissue lesion size change (disease progression) At least a 20% increase in size of lesion taking as reference the baseline diameter of the lesion [32].

Soft tissue lesion size change (treatment response) at least a 30% decrease in the size of lesion, taking as reference the baseline diameter or disappearance of the lesion [32].

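### Soft-tissue and bone size change is set by percentage alone, so for non-nodal soft-tissue lesions under 10 mm the cut-offs fall inside the trial's own nodal measurement variation

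*Protocol article*

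**What the plan says.** All of this is in the Protocol article, Derivation of enhanced reference standard, and the threshold list that closes it.

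- **Nodes:** "Increase of ≥2 mm and decrease of ≥3 mm in short axis diameter on contrast enhanced mDixon sequence will be considered true change". The stated basis is: "Based on unpublished data from repeatability studies carried out as part of the LOCATE trial".
- **Soft tissue, progression:** "At least a 20% increase in size of lesion taking as reference the baseline diameter of the lesion".
- **Soft tissue, response:** "at least a 30% decrease in the size of lesion, taking as reference the baseline diameter or disappearance of the lesion".
- **Bone, progression:** "≥ 25% increase in size (sum of short and long axes diameters) of lesions on CT, or MRI".
- **Bone, response:** "≥ 50% decrease in size (sum of short and long axes diameters) of lesions on CT/ MRI", or normal signal on MRI.
- **PSA progression:** a relative part (25%) and an absolute part (2 ng/mL), both required and confirmed on a second reading.

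These cut-offs decide the reference label when WB-MRI was positive at baseline and conventional imaging was negative. Growth with a PSA rise makes the scan a true positive; growth without one makes the patient unknown. The scan is a false positive when the lesion "resolved or reduced in size at follow-up (in the absence of systemic therapy) regardless of PSA change".

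**The concern.** The list treats measurement error in two ways. Nodal limits are chosen so that a change beyond them is unlikely to be noise, and PSA progression pairs a percentage with an absolute amount. Soft tissue and bone have neither safeguard. A fixed percentage of a small diameter is a very small distance, so a stable lesion can cross the line because it was measured twice.

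Here the cut-offs define truth; they do not merely describe response. A real metastasis that measures smaller by chance in an untreated man moves from true positive to false positive, which lowers both the sensitivity and the specificity of WB-MRI. A benign lesion that measures larger by chance, in a man whose PSA is progressing for another reason such as local recurrence, becomes a true positive and so also a miss for conventional imaging. The labels feed the per-patient accuracy results and the true/false positive and negative outcomes in the economic model.

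**Working it through.** **Inputs from the threshold list.** Nodal limits +2 mm and -3 mm (95%); soft tissue +20% and -30% of diameter D; bone +25% and -50% of the two-axis sum S. The nodal limits cannot be reproduced, because the article gives no standard deviation or sample size for them.

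**Step 1: where the percentage falls below the nodal limit (soft tissue).**
- Growth: 0.20 × D < 2 mm when D < 2/0.20 = 10 mm.
- Shrinkage: 0.30 × D < 3 mm when D < 3/0.30 = 10 mm.

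Both directions cross at the same size.

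**Step 2: chance that an unchanged soft-tissue lesion crosses.** Assume normal error of the same size as for nodes. Two readings agree with both nodal limits at 2.5% per side:
- Reading A, no bias, separate spread per direction: SD up = 2/1.96 = 1.02 mm; SD down = 3/1.96 = 1.53 mm. Then P(grown) = 1 - Φ(0.20D/1.02) and P(shrunk) = Φ(-0.30D/1.53).
- Reading B, limits of agreement from -3 to +2 mm: bias = -0.5 mm; SD = 2.5/1.96 = 1.28 mm. Then P(grown) = 1 - Φ((0.20D + 0.5)/1.28) and P(shrunk) = Φ((-0.30D + 0.5)/1.28).

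| D (mm) | Cut-offs (mm) | Grown, A | Grown, B | Shrunk, A | Shrunk, B |
|---|---|---|---|---|---|
| 5 | +1.0 / -1.5 | 16.4% | 12.0% | 16.4% | 21.7% |
| 6 | +1.2 / -1.8 | 12.0% | 9.1% | 12.0% | 15.4% |
| 8 | +1.6 / -2.4 | 5.8% | 5.0% | 5.8% | 6.8% |
| 10 | +2.0 / -3.0 | 2.5% | 2.5% | 2.5% | 2.5% |
| 15 | +3.0 / -4.5 | 0.2% | 0.3% | 0.2% | 0.1% |

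**Step 3: bone.** The nodal limit is carried to a sum of two axes by √2 if the axis errors are independent, or by 2 if they are fully correlated.
- Growth: 2√2/0.25 = 11.3 mm to 4/0.25 = 16 mm. The rule lies inside the noise only for sums below about 11-16 mm.
- Shrinkage: 3√2/0.50 = 8.5 mm to 6/0.50 = 12 mm.
- A 5 x 5 mm lesion (S = 10 mm) is called grown in about 3-11% and shrunk in about 1-6%. At 10 x 10 mm both are below 1%.

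**Step 4: effect of a minimum.** With floors of 2 mm up and 3 mm down for soft tissue, the noise-only rate for any lesion under 10 mm is 2.5% in each direction under either reading. At 10 mm and above nothing changes.

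**Step 5: from a size call to a label.** Shrinkage in a man without systemic therapy leads straight to false positive. Growth needs confirmed PSA progression as well, so the growth percentages in Step 2 are not true-positive rates.

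**The case against.** Much can be said on the other side.

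- **Few lesions may be involved.** Nodes keep their millimetre limits, so the 20%/30% rule reaches only non-nodal soft tissue. Table 2 describes features for nodes and bones only, and the article gives neither the number nor the size of other soft-tissue lesions. This stands, and it rules out any estimate of affected patients.
- **Growth is protected.** A reader might infer that noise-only growth is scored as a true positive. The text does not support that: without confirmed PSA progression the patient is unknown. Shrinkage has no such protection.
- **Bone is hardly touched.** A reader might put bone on the same footing as soft tissue. Step 3 does not support that, least of all for the 50% shrinkage rule.
- **The noise is borrowed.** The nodal limits are for the short axis on contrast-enhanced mDixon. Error in other tissue, or on CT, may differ. This stands as an assumption.
- **Higher rates could be quoted.** An SD of 1.28 mm with no bias gives 22% growth at 5 mm, but it also puts 5.8% of unchanged nodes beyond +2 mm, which contradicts the nodal limit. It is not used here.
- **The cut-offs come from cited criteria, and judgement is applied.** Those sources may carry a minimum, but the rule as adopted here states none. Thresholds are read in the context of treatment, and discrepant findings go to a consensus panel (12-month follow-up WB-MRI). Neither provision states a size rule, so they reduce the problem without removing it.

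**Conclusion.** The point holds in a limited form. The plan fixes soft-tissue and bone change by percentage alone, and for non-nodal soft-tissue lesions under 10 mm those percentages lie inside the variation the trial itself reports for nodes. If soft-tissue error is like nodal error, noise alone produces a growth / shrinkage call in about 12-16% / 16-22% of repeats at 5 mm, 9-12% / 12-15% at 6 mm and 5-6% / 6-7% at 8 mm, against 2.5% / 2.5% at 10 mm. The main exposure is shrinkage in untreated men. Growth is secondary and bone growth minor.

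A reader might go further and conclude that the primary sensitivity and specificity are materially wrong. The document does not support that, because it does not show how many men would have their label decided by such a lesion. The case for change is that a rule defining the reference standard should not be looser for one tissue than the trial's own evidence allows for another.

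**What to change.** Amend the threshold list so that both a percentage and an absolute change are required:

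- **Soft tissue:** at least 20% and at least 2 mm for an increase; at least 30% and at least 3 mm for a decrease. Use the tissue-specific limit instead if the trial's repeatability data provide one.
- **Bone growth:** at least 25% and at least the repeatability limit for the two-axis sum. Carried over from nodes this is about 2.8-4 mm (2√2 to 2 × 2); a limit measured in bone is preferable.
- **Label:** state that a lesion not meeting both parts counts as unchanged, and say how a patient with an unchanged WB-MRI-positive lesion is classified. The text gives no label for this case (check Fig. 2, which was not available for this review). One option is unknown, with a sensitivity analysis that assigns these patients each way.

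The cost is a clause in the threshold list and one line on the label. No new scans are needed, and the Study status section says full analysis had not begun. The downside is that some small real changes will count as unchanged, and somewhat more patients may be unclassified.
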